**5. Expected research duration**

From the approval of the study protocol by the institutional review board to December 2016

**6. Subjects of research**

Patients who underwent coronary angiography for coronary artery disease or peripheral artery disease

**7. Background and object**

**1) Background**

The prevalence of cardiovascular disease is increasing and it is a major cause of death. Therefore, transarterial examinations such as coronary angiography and intervention has become important tools of diagnosis and treatment for cardiovascular disease. The procedures are usually performed through radial or femoral artery. And hemostasis after procedure is an important issue. Direct external compression on punctured site takes long time to control bleeding can cause discomfort to patients.^1^ Also, the success rate of hemostasis with this method was low. To overcome this problem, compression devices have been developed and used in the clinical field.^2-4^ HemCon^®^ pad (HemCon Medical Technologies, Inc., Portland OR, USA) is a world-widely applied hemostatic device, which is based on synthetic chitosan made from chitin.^5^ Chitin is obtained easily from shellfish and insects, and the mechanism of action is based on ionic interaction between the positively loaded chitosan and negatively loaded red blood cells and platelets. Recently, a domestic company developed a chitosan-based pad, named ezClot^®^ (Soyeon, Seongnam-si, Korea) and it was manufactured similar with HemoCon^®^ pad. The ezClot^®^ was approved by Korean Food and Drug Administration. Therefore, our study evaluates the safety and hemostatic effect of ezClot^®^.

[figure not shown]

**2) Hypothesis and object**

For radial subgroup, we hypothesized that the combination of compression device (CD) with chitosan-based pads would improve hemostasis efficacy and safety compared with control devices after coronary angiography or interventions.

For femoral subgroup, we hypothesized the ezClot pads would show similar hemostasis efficacy compared to BloodSTOP^®^ ix pads.

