**iii) Sample size**

This trial is a proof-of-concept trial. To prove the hypothesis that the study arm has better or equal hemostasis efficacy than the control arm, this study will enroll a total of 315 patients.

- Femoral puncture subgroup: Study arm 100 patients + control arm 50 patients

- Radial puncture subgroup: Study arm 100 patients + control arm 50 patients

Number considered the rate of drop out (5%): Study arm 210 patients,

Control arm 105 patient

🡪 total 315 patients

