**10. Research Methods**

**i) Detailed descriptions of the protocols**

Before coronary or peripheral angiography, the potential candidates will be screened. Participant will give their written informed consents before the procedures. Decision of the participation into the study will be decided immediately after the procedures. Study patients will be stratified into the radial or femoral subgroups.

Study patients will be randomly assigned to the study or control groups in a 2:1 fashion after completion of the procedures. Random sequence will be generated using a computer random number generator. The allocation numbers will be kept in a locked unreadable computer file, and could be accessed only after the characteristics of an enrolled participant have been entered.

The primary endpoint is time to hemostasis. The Secondary endpoints include bleeding, hematoma, pseudoaneurysm, vessel occlusion, dissection, urgent surgical repair, vasovagal reaction, and allergic skin reaction.

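### The femoral aim of similar or equal hemostasis has no margin, so 100 versus 50 patients cannot deliver the proof the protocol promises

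*Protocol*

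**What the plan says.** The protocol gives the two access strata different hypotheses (section 7, Hypothesis and object). The radial hypothesis is improvement over the control. The femoral one is a comparison with an active pad: "For femoral subgroup, we hypothesized the ezClot pads would show similar hemostasis efficacy compared to" BloodSTOP ix.

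Section 9, Sample size, opens with "This trial is a proof-of-concept trial". The next sentence gives the purpose of the 315 patients: "To prove the hypothesis that the study arm has better or equal hemostasis efficacy than the control arm". The femoral allocation is "Femoral puncture subgroup: Study arm 100 patients + control arm 50 patients", and a 5% dropout allowance is then added.

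Section 10 fixes the endpoint: "The primary endpoint is time to hemostasis". Nowhere does the protocol give an equivalence or non-inferiority margin, define similar or equal, or state a significance level, power, SD, expected time to hemostasis, test or success rule.

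**The concern.** Equality cannot be demonstrated by a trial of any size. A trial can only show that the difference is smaller than some limit fixed in advance. That limit defines the hypothesis and determines how many patients are needed. Here the number is fixed and said to serve as proof, while the limit is missing.

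With no limit, the easiest way to claim similarity is to observe that a difference test was not significant. That criterion rewards imprecision, since a smaller or noisier trial meets it more easily. The femoral stratum is half of the planned sample and similarity is its stated hypothesis, so its main conclusion would have no sound basis. A margin chosen after the outcomes are known would not repair this.

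**Working it through.** **Inputs from the protocol**
- Femoral arms 100 and 50, dropout 5%, total 315 (section 9, Sample size).
- Allocation 2:1 and primary endpoint time to hemostasis (section 10).

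**Inputs assumed, because the protocol gives none**
- Two-sided 5% test, equivalently one-sided 2.5% for non-inferiority.
- Comparison of means with a normal approximation and a common SD. Results are in SD units.
- Exactly 100 versus 50 analysed.
- A positive difference means that ezClot is slower.

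**Step 1. Reproduce the stated total.** 200 × 1.05 = 210 and 100 × 1.05 = 105, together 315, as stated. The base of 100 + 50 per stratum cannot be reproduced, since nothing is given from which to derive it.

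**Step 2. Precision.** SE = √(1/100 + 1/50) = √0.03 = 0.1732 SD. The 95% confidence interval half-width is 1.96 × 0.1732 = 0.34 SD.

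**Step 3. How often would a truly slower pad give a non-significant result?** For a true deficit d, the probability is 1 − [Φ(d/SE − 1.96) + Φ(−d/SE − 1.96)].

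| True deficit | d/SE | Non-significant |
| --- | --- | --- |
| 0.2 SD | 1.155 | 79% |
| 0.3 SD | 1.732 | 59% |
| 0.4 SD | 2.309 | 36% |
| 0.5 SD | 2.887 | 18% |

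The probability falls to about one half at d = 1.96 × 0.1732 = 0.34 SD. Non-significance is the more likely result only for deficits below that.

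**Step 4. What margin could this size support?** If the pads are truly equal, non-inferiority power is Φ(margin/SE − 1.96).

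| Margin | Power |
| --- | --- |
| 0.2 SD | 21% |
| 0.3 SD | 41% |
| 0.4 SD | 64% |
| 0.5 SD | 82% |

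For 80% power the margin must be (1.96 + 0.8416) × 0.1732 = 0.49 SD. For 90% power it must be (1.96 + 1.2816) × 0.1732 = 0.56 SD. Two-sided equivalence, with two one-sided tests at 2.5%, needs about 0.56 SD and 0.62 SD respectively.

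**Step 5. What would a narrower margin need?** At 80% power and 2:1, the control arm is 1.5 × (1.96 + 0.8416)² / margin² = 11.77 / margin², rounded up. The femoral total is three times that, before dropout.

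| Margin | Control arm | Femoral total |
| --- | --- | --- |
| 0.5 SD | 48 | 144 |
| 0.4 SD | 74 | 222 |
| 0.3 SD | 131 | 393 |
| 0.2 SD | 295 | 885 |

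The planned 150 meets only the first of these.

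**The case against.** **No rule is written.** A reader might infer that the trial plans to treat a non-significant p-value as proof of similarity. The protocol does not say so. It names no test and no success criterion, and those may properly stand in a statistical analysis plan that is not shown. This stands: the misuse is permitted, not prescribed. It does not remove the point, because the protocol itself fixes the number of patients and says what that number is to prove.

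**The two wordings need not conflict.** A reader might infer that the sample size section turns a two-sided similarity aim into one-sided non-inferiority. The sentence introduces the total for both strata, so it can equally be shorthand for better in the radial stratum and equal in the femoral one. The text does not settle this. On either reading, equal remains undefined.

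**The trial is labelled proof-of-concept.** This softens the ambition and suits an estimate with a confidence interval. The next sentence nevertheless speaks of proof, so the label does not cure the overclaim.

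**The effect sizes are not the protocol's.** This also stands. The document gives no SD and no clinically relevant difference, so nothing shows that 0.3 SD is material. Time to hemostasis may be skewed, and simple randomization (section 10, Randomization method) does not guarantee exactly 100 versus 50. The figures are therefore indicative and are shown over a range.

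**Conclusion.** The point holds in a limited form. The femoral claim of similar or equal efficacy has no margin, so the planned 100 versus 50 cannot deliver the proof that the sample size section promises. This is more than a detail left to an analysis plan, because a margin sets both the hypothesis and the sample size.

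Under the stated assumptions, the stratum can support a non-inferiority claim with 80% power only if a loss of roughly half an SD is acceptable, which the protocol never says. It would be too strong to conclude that a materially slower pad would more often than not pass as similar. That is true only for deficits below about 0.34 SD; larger ones would usually be detected.

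**What to change.** **Preferred.** In section 7 (Hypothesis and object) and section 9 (Sample size), replace the femoral aim of proof with an estimation aim. Report the difference in time to hemostasis with its 95% confidence interval (expected half-width about 0.34 SD), and state that a non-significant test will not be read as similarity. This fits the proof-of-concept label and needs no extra patients.

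**Alternative.** If a margin of about 0.49 SD or wider can be justified before any outcome is seen, state it in both sections, and judge the upper limit of the 95% confidence interval for the difference (ezClot minus control) against it. A two-sided reading of similar would need about 0.56 SD for the same power. A narrower margin would be underpowered at this size, and the protocol should then say so; reaching 80% power would take the larger femoral totals shown in the working.

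**Cost.** For the estimation option, wording in two sections and a less favourable claim. The alternative also avoids extra patients only if the justified margin is wide enough, so the change cannot be called free under every option.

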**8. Study materials and devices**

- Study device : ezClot^®^ (Chitosan-based pad)
- Control device :

① Femoral puncture subgroup: BloodSTOP^®^ ix
(soluble, oxidized–etherified regenerated cellulose)

② Radial puncture subgroup: manual compression with compression device

**9. Inclusion/exclusion criteria**

**i) Inclusion criteria**

patients aged ≥18 years

Those with elective or urgent coronary angiography or interventions

**ii) Exclusion criteria**

congenital or acquired bleeding tendency

thrombocytopenia (platelet count < 50,000/uL)

patients with hypersensitivity for shellfish

**iii) Sample size**

This trial is a proof-of-concept trial. To prove the hypothesis that the study arm has better or equal hemostasis efficacy than the control arm, this study will enroll a total of 315 patients.

- Femoral puncture subgroup: Study arm 100 patients + control arm 50 patients

- Radial puncture subgroup: Study arm 100 patients + control arm 50 patients

Number considered the rate of drop out (5%): Study arm 210 patients,

Control arm 105 patient

🡪 total 315 patients

**iv) Patient recruitment**

This study will recruit the patients who were admitted to perform invasive procedure for cardiovascular diseases. If the patient is suitable for this study, the researcher will explain the purpose of study and provide written consent to the patients and patients’ guardians. The principal researcher and research institution do not exclude the patients distinguishing from race, economic state. If the patients are suitable for inclusion criteria, we help them to participate in the research.

**10. Research Methods**

**i) Detailed descriptions of the protocols**

Before coronary or peripheral angiography, the potential candidates will be screened. Participant will give their written informed consents before the procedures. Decision of the participation into the study will be decided immediately after the procedures. Study patients will be stratified into the radial or femoral subgroups.

Study patients will be randomly assigned to the study or control groups in a 2:1 fashion after completion of the procedures. Random sequence will be generated using a computer random number generator. The allocation numbers will be kept in a locked unreadable computer file, and could be accessed only after the characteristics of an enrolled participant have been entered.

The primary endpoint is time to hemostasis. The Secondary endpoints include bleeding, hematoma, pseudoaneurysm, vessel occlusion, dissection, urgent surgical repair, vasovagal reaction, and allergic skin reaction.

**ii) Randomization method**

control arm : Femoral puncture group : BloodSTOP^®^ ix

Radial puncture group : manual compression with compression device

We randomized with world wide web <http://stattrek.com/Tables/Rsndom.aspx> (study device = 1/ control = 0). Randomization was followed simple randomization.

**iii) Devices utilizing method**

Hemostasis is performed by compression to all patients. However, the selection of devices is randomized. The manual of study device, ezClot^®^ is as follows:

- 1.
[figure not shown]
Pad type

[figure not shown]

[figure not shown]
Bandage type

**iv) Study endpoints**

- Primary end point : time to hemostasis

- Secondary end point : vascular complication after hemostasis

- Bleeding (TIMI definition: major, minor, minmal)

- Hematoma

- Retroperitoneal hematoma

- Pseudoaneurysm

- Vessel occlusion

- Dissection

- Surgical repair

- Vasovagal reaction

**i) Schematic protocol**

| Variables | Baseline | Follow Up | |
| --- | --- | --- | --- |
|  |  | Post-Procedure (1day) | 30 days(±2w) |
| History taking | O | O | O |
| Physical examination | O | O | O |
| CBC | O | O | O |
| Time to hemostasis | O | X | X |
| Hemorrhage, hematoma, pseudoaneurysm | O | O | O |
| Distal flow | O | O | O |
| Subjective discomfort | X | O | X |

